## 3. Study Objectives and Study Design

A protocol of clinical trials was developed following the guidelines of Standard Protocol Items: Recommendations for Interventional Trials (SPIRIT) [32]. The checklist for SPIRIT can be seen in Supplementary Material 1.

The objective of this study is carried out to assess the reduction of proinflammatory cytokines after TENS application in patients with breast cancer. A nonrandomized, open, single-arm clinical trial with paired analysis will be developed. The study design is described in Figure 1.

A minimum of 59 patients is expected. All subjects will receive a single application of TENS for 30 minutes. Assessments will be made before and after application. Screening data will be reviewed to determine subject eligibility. Individuals who meet all of the inclusion criteria and none of the exclusion criteria will be included in the study. The total duration of the subject's participation will be one day (time to complete all study evaluations).

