## 4. Criteria for Evaluation

The endpoints for the study are described below:

*Primary Endpoint*. The primary endpoint is to analyze the reduction in blood concentration of proinflammatory cytokines.

*Secondary Endpoint*. The secondary endpoints are to analyze the effect size according to each type of proinflammatory cytokine, describe the effect size of the reduction according to breast cancer immunohistochemistry, and analyze the effect on anti-inflammatory cytokines.

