## 6. Study Intervention

The consent form will be obtained as the first procedure from all participants by the study coordinator. The confidentiality of the data will be guaranteed until the end of the research.

The study will not be randomized. All patients will be submitted to TENS intervention, and the data will be analyzed in the pre- and postintervention of each patient.

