## 8. Statistical Methods

### 8.1. Sample Size

The sample size was based on the calculation of the sample size in pilot studies proposed by Viechtbauer et al. [36]: 5% probability with 95% confidence level resulted in a sample requiring 59 participants.

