### 8.2. Statistical Analysis

For the characterization of the sample, a descriptive analysis of the data will be performed; therefore, the qualitative variables will be described by absolute and relative frequency; the quantitative variables that present normal distribution according to the Shapiro-Wilk test (*p* ≥ 0.05) will be presented as means, standard deviations, and 95% confidence intervals, while those that do not present normal distribution according to the Shapiro-Wilk test (*p* < 0.05) will be presented as medians and respective 95% confidence intervals and 25th and 75% percentiles.

To analyze the quantitative variables between the groups, Student's *t*-test will be used for variables that have a normal distribution and the Mann-Whitney test will be used for variables that do not have a normal distribution.

The confidence level adopted for all analyses will be 95%. All analyses will be performed using the Data Analysis and Statistical Software for Professionals (Stata) version 11.0®.

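### Section 8.2 names between-group tests, including Mann-Whitney, for a single-arm trial whose pre/post comparison is paired

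*Protocol article*

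**What the plan says.** Section 3 of the protocol article fixes the design: "A nonrandomized, open, single-arm clinical trial with paired analysis will be developed". Section 6 repeats that there is no randomisation, that all patients receive TENS, and that "the data will be analyzed in the pre- and postintervention of each patient". Section 7.2 describes two blood draws from the same woman, before and after one 30-minute session. Section 4 sets the main question: "The primary endpoint is to analyze the reduction in blood concentration of proinflammatory cytokines".

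Section 8.2 then gives the tests. The sentence opens "To analyze the quantitative variables between the groups" and assigns Student's t-test to normally distributed variables; for the rest, "the Mann-Whitney test will be used for variables that do not have a normal distribution". The groups are not defined. No paired t-test, Wilcoxon signed-rank test or other within-patient method is named anywhere in the article. Normality is to be judged by a Shapiro-Wilk test on each quantitative variable.

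On sample size, section 8.1 says "5% probability with 95% confidence level resulted in a sample requiring 59 participants".

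**The concern.** The trial has no treatment groups, so the most natural reading of the groups in section 8.2 is the pre and post samples. These are two measurements on the same woman, taken about half an hour apart. Mann-Whitney, and the t-test in its two-sample form, compare two independent sets of people. Applied to paired values, they set the mean change against the spread between women, when the relevant spread is that of the within-woman change. Removing the between-woman spread is the main statistical advantage of this design.

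An analyst who follows section 8.2 literally would therefore get wrong p-values for the primary endpoint and could overlook a real reduction. Section 10 also says that the results will be used to size later trials. If the variability carried forward is the between-patient one, those calculations would start from the wrong variance.

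**Working it through.** **Inputs.** From the document: n = 59 pairs (sections 3 and 8.1) and a 95% confidence level (section 8.2). The side of the test is not stated; two-sided alpha 0.05 is assumed. The document gives no pre/post correlation, SD or effect size. The correlation r is therefore varied from 0 to 0.9, and the change d is set at 0.2, 0.3 and 0.5 in units of the SD at one time point.

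**The plan's own figure.** The pilot-study formula is n = ln(1 - 0.95)/ln(1 - 0.05) = 58.40, rounded up to 59. This matches section 8.1. It contains no effect size, SD, correlation or power, so it does not depend on which test is used.

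**Standard error.** With SD s at each time point, the true standard error of the mean change is s·sqrt(2(1-r)/n). The two-sample formula uses s·sqrt(2/n). The ratio is 1/sqrt(1-r). At r = 0.5 and s = 1 this is sqrt(2/59) = 0.184 against sqrt(1/59) = 0.130, a ratio of 1.41.

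**Type I error of the unpaired tests**, nominal 5%, by simulation (20,000 runs for the t-test, 3,000 for Mann-Whitney):

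| r | SE ratio | Unpaired t | Mann-Whitney |
|---|---|---|---|
| 0 | 1.00 | 4.9% | 4.8% |
| 0.3 | 1.20 | 1.8% | 2.1% |
| 0.5 | 1.41 | 0.6% | 0.5% |
| 0.7 | 1.83 | 0.1% | 0.1% |
| 0.8 | 2.24 | about 0.01% | about 0% |

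**Power, with paired power held at 80%.** At n = 59 this needs a change of 0.371 SDs of the within-patient difference, so the paired statistic has mean 0.371 × sqrt(59) = 2.85. The unpaired statistic has mean 2.85·sqrt(1-r), SD of about sqrt(1-r), and a critical value of about 1.98 (t with 2 × 59 - 2 = 116 degrees of freedom). At r = 0.5 the mean is 2.02 and the SD 0.71, so the standardised distance is (1.98 - 2.02)/0.71 = -0.06 and power is about 52%. Simulation (4,000 runs) gives:

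| r | Unpaired t | Mann-Whitney |
|---|---|---|
| 0.3 | 68% | 65% |
| 0.5 | 52% | 49% |
| 0.7 | 23% | 22% |
| 0.8 | 6% | 6% |

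The change in raw units is 0.371·sqrt(2(1-r)), so it shrinks along this table: 0.44 SD at r = 0.3, 0.37 at 0.5, 0.29 at 0.7 and 0.23 at 0.8.

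**Power, with the raw change held fixed** (paired t / unpaired t):

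| r | d = 0.2 | d = 0.3 | d = 0.5 |
|---|---|---|---|
| 0 | 19% / 19% | 36% / 36% | 76% / 76% |
| 0.3 | 25% / 15% | 48% / 34% | 89% / 81% |
| 0.5 | 33% / 11% | 62% / 32% | 97% / 85% |
| 0.7 | 50% / 6% | 83% / 27% | 99.8% / 90% |
| 0.8 | 67% / 3% | 95% / 23% | 100% / 94% |

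The rank tests behave in the same way: at d = 0.3 and r = 0.7, Wilcoxon signed-rank has 81% power and Mann-Whitney 26%.

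**The case against.** **The text may not mean what it seems to mean.** Student's t-test has a paired form, and section 3 promises a paired analysis. A reader might infer that the plan commits to unpaired tests in both branches. It does not say so: the t-test branch is wrong only if run in its two-sample form, as the between-group wording suggests. Mann-Whitney has no paired form, so that branch cannot be rescued in this way.

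**The groups could be the immunohistochemistry subgroups.** The named tests could then fit, and the primary test might sit in a document not shown. But section 4 asks only to describe effect sizes by subgroup, so this is not the natural reading. It would also leave the article's only sentence on testing silent about its primary endpoint.

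**The cost in power can be overstated.** A reader might infer that most of the power is lost, or that a real reduction would usually be missed. That holds only at r of about 0.7 or more with a modest change. At r = 0 nothing is lost, and at d = 0.5 the unpaired t-test keeps 85% to 94% for r from 0.5 to 0.8. The document supplies neither quantity, so no single loss can be claimed.

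**Confidence intervals.** A reader might also infer that the planned intervals are wrong. The intervals in section 8.2 are descriptive, for the mean or median of each variable, and pairing does not affect them. The factor 1/sqrt(1-r) would apply only to an unpaired interval for the pre/post difference, which the article does not plan.

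**The simulated data are normal, whereas Mann-Whitney is reserved for non-normal variables.** This stands in part. Mann-Whitney depends only on ranks, so its figures also hold for log-normal concentrations with d read on the log scale. Other shapes were not examined.

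**Conclusion.** The contradiction is real, and section 8.2 is wrong as written. Sections 3 and 6 define a paired comparison in a single arm, while the only tests named are between-group tests, one of them unambiguously for independent samples. If section 8.2 is followed for the pre/post comparison, the p-values for the primary endpoint are wrong whenever the two values are correlated.

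With positive correlation the error is conservative. True type I error falls from 5% to about 2% at r = 0.3, 0.6% at 0.5 and near zero at 0.8. The loss of power ranges from none (r = 0) through 12 points (97% to 85% at r = 0.5, d = 0.5) to 56 points (83% to 27% at r = 0.7, d = 0.3), and more at higher correlation. These sizes rest on assumed values of r and d, equal SDs before and after, and a two-sided 5% level.

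**What to change.** Replace the sentence on tests in section 8.2 with:

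*Pre- and post-intervention concentrations will be compared within patients using the post-minus-pre change: paired t-test if the within-patient differences (log-transformed if needed) are approximately normal, otherwise the Wilcoxon signed-rank test, each with a 95% CI for the within-patient change.*

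Normality then has to be judged on the differences, not on the pre and post values separately. Two-group tests should be kept only for comparing changes between immunohistochemistry subgroups, and the groups named.

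The cost is one sentence before analysis. It needs no extra data, blood draws or patients. The sample size of 59 was not derived from a test and need not change for this reason.

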## 9. Ethical and Regulatory Considerations

The study was approved by the Independent Ethics Committee (Centro Universitário FMABC, Brazil) and is also registered in the Brazilian Clinical Trials (Search text: RBR-10jbwh47).

Ethical considerations will be based on the use of biological material for scientific purposes, with confidentiality of identity, free from coercion or conflict of interest of the institution or of people involved in the project.

The collections will respect the technical protocols of the services involved. Research participants will be previously informed of the therapy by TENS and blood collection. The analysis of these data will only happen under the consent in a specific form (Informed Consent Form (ICF)), according to resolution 466/2012 of the National Health Council. The present project has been already approved by the Ethics Research Committee.

## 10. Discussion

TENS acts on afferent nerve fibers blocking the nerve transmission of pain—an effect known as gate theory [37]—or stimulating the release of opioids through the central nervous system [12, 37]—both action mechanisms are already described to analgesia.

Regarding studies with TENS and pain reduction [1–5], the results evidence that there is a reduction in pain intensity when compared to control groups in a variety of diseases. When evaluating studies related to pain intensity, it is observed that less intense pain also has fewer cytokines [7, 9, 10]. The action mechanism through blocking pain (gate theory) may induce the reduction in cytokines.

In order to test this hypothesis of the pain blockade (TENS)/cytokine pathway, we developed a systematic review with meta-analysis [11]. The effect of reducing cytokines was statistically significant, but in detriment of the few researches, it was unable to determine the consistency of this effect and the action mechanism involved in this result. Due to the heterogeneity of the clinical trials found, we cannot rule out that the results could be related to another TENS action pathway (opioid release by the central nervous system)

The researches indicate that acupuncture or electroacupuncture facilitates the release of certain neurotransmitters, especially opioids [38]. The same opioid release is described as an action mechanism of TENS current by electrodes [37, 39]. These opioids act on the central nervous system and activate the sympathetic or parasympathetic nervous system [37, 38].

As opioid receptors are also present on immune cells, TENS-induced opioid release could directly modulate these cells (neuroimmune interaction) [38]. The activation of the parasympathetic nervous system releases acetylcholine (the main neurotransmitter), which by stimulating macrophages can inhibit the production of several proinflammatory cytokines TNF-*α*, IL-1, and IL-6 [6, 40].

The systemic inhibition of immunity via parasympathetic flow is the path that would explain the anti-inflammatory effect of several nonpharmaceutical modalities (e.g., acupuncture, biofeedback, and placebo effect) [41]. We hypothesized that TENS works by systemic inhibition and that cholinergic interactions would lead to the reduction of proinflammatory cytokines that we found in our systematic review. And in order to test this hypothesis, we chose a disease mediated by cytokines but without the pain bias.

Recent research indicates that the neoplasic environment arises from sites of infection, chronic irritation, and inflammation and that inflammation is a component of tumor progression. Coussens and Werb, cited by Kavoussi and Ross [41], report that the tumor microenvironment is largely influenced by inflammatory cells, and this process would be responsible for proliferation, survival, migration, and metastasis.

The primary objective of this protocol is to assess whether TENS can reduce proinflammatory cytokines in an inflammatory disease. Cancer was chosen as the study pathology, considering that studies describe that the chronic inflammation present in the tumor microenvironment increases the risk of developing or disseminating cancer [20–23]. Among the types of cancer that could be studied, we chose breast cancer because it is one of the carcinomas with higher incidence and has the worst prognosis when related to increased inflammatory activities [20, 21, 28–31].

Our hypothesis is that if we have a successful conclusion of the proposed clinical trial, we will identify this anti-inflammatory effect on TENS possibly related to a parasympathetic nerve pathway. We pretend to explore the results and calculate the sample size for other clinical trials that can test and increase the power of evidence of TENS (anti-inflammatory effect) in the treatment of inflammatory diseases.

## Figures and Tables

**Figure 1 fig1:**
[figure not shown]
Trial flow diagram.

**Figure 2 fig2:**
[figure not shown]
Demonstration of the TENS application site.

**Table 1 tab1:** Eligibility criteria.

Inclusion criteria
(i) Written informed consent obtained from the subject (ii) Adult women (≥18 years of age) (iii) Primary diagnosis of breast cancer confirmed by immunohistochemistry and breast biopsy (iv) Medical indication but having not started chemotherapy
Exclusion criteria
(i) Metastatic disease, breast cancer recurrence, or mastectomy (ii) Bilateral breast cancer (iii) Chemotherapy, biological therapy, radiation therapy, or previous surgery for any active malignancy, including breast cancer (iv) No biological therapy even if indicated for another pathology (v) Another malignancy in the last 5 years (vi) Any pathology in the cervical spine and shoulders, even if asymptomatic (vii) Any inflammatory disease and/or orthopedic disease in activity (viii) Physical therapy or acupuncture sessions ongoing for any pathology (ix) Heart failure (New York Heart Association) grade III or IV, myocardial infarction, coronary/peripheral artery revascularization, stroke, unstable angina pectoris, uncontrolled arrhythmia, or pulmonary embolism (x) Active infection (xi) Uncontrolled diabetes mellitus (xii) Uncontrolled hypertension (blood pressure > 150/100 mmHg) (xiii) Major surgery or significant traumatic injury lesser than 6 months

**Table 2 tab2:** TENS parameters.

Current	TENS
VIF (variable intensity and frequency)	Turn on
Frequency—R (Hz)	2-247 Hz
Pulse size—T (*μ*s)	50-500 *μ*s
Intensity (mA)	Maximum tolerated by the patient
Time	30 minutes

## Data Availability

The data used to support the findings of this study may be available upon request to the authors, who can be contacted by e-mail.

## Abbreviations

CA: Cancer
D1: Day 1 of treatment
ES: Effect size
EDTA: Ethylenediaminetetraacetic acid
ELISA: Enzyme-linked immunosorbent assay
Hz: Hertz
IL-1*β*: Interleukin 1*β*
IL-1*α*: Interleukin 1*α*
IL-2: Interleukin 2
IL-4: Interleukin 4
IL-6: Interleukin 6
IL-7: Interleukin 7
IL-10: Interleukin 10
IL-13: Interleukin 13
*μ*s: Microsecond
mA: Milliampere
SPIRIT: Standard Protocol Items: Recommendations for Interventional Trials
TENS: Transcutaneous electrical nerve stimulation
TGF-*β*: Transforming growth factor *β*
TNF-*α*: Tumor necrosis factor alpha
VIF: Variable intensity and frequency
WIC: Written informed consent.
